### Concealment mechanism {16b}

We will make use of a central telephone randomisation system, where the allocation sequence is only available to the secretariat of the Department of Dietetics. The investigator will contact the secretariat by phone, when a group of ten patients is complete and has signed the informed consent forms, to receive the allocation of the group.

### Implementation {16c}

The allocation sequence generated by the statistician will be kept in a secure place in the dietetics department secretariat of the different study sites, where only the secretary has access to the randomisation list. When a group of ten patients is complete, the researcher will contact the secretary of that study site by telephone to obtain the allocation, after which the patients of that group will be enrolled by the researcher.

### Assignment of interventions: blinding

#### Who will be blinded {17a}

Given the nature of the intervention, the participants could not be blinded. Due to practical reasons, we elected not to blind investigators and medical staff. However, the first preliminary statistical analyses of the primary outcome will be performed by an independent statistician, blinded to the allocation.

### Procedure for unblinding if needed {17b}

The design is open label with only data analysts being blinded, so un-blinding will not occur.

### Data collection and management

#### Plans for assessment and collection of outcomes {18a}

Outcome data will be collected in a case report form designed in a data management system (Castor EDC®). Questionnaires will be sent digitally to participants using Castor EDC®. To promote data quality of the measurements, all researchers will be trained to perform the measurements. To ensure the data quality of the questionnaires, these will be checked by the researcher to see if there are any irregularities.

Study instruments used:Weight will be measured using a Seca 888 compact digital flat scaleCosts will be measured by the Trimbos/iMTA Questionnaire for Costs (TiC-P)Quality of life will be measured with the EuroQol questionnaire EQ-5D-5LBlood pressure will be measured using the Omron, M4-IFood intake will be measured using dietary history [27]Physical activity will be measured by wearing an Activ8 sensor (BV, Valkenswaard, The Netherlands) for 1 week. The sensor will measure non-wear, sitting, standing, walking, cycling, or running in counts per 20 sWaist circumference will be measured with a centimetreBody composition will be measured with the Bodystat Quadscan 4000, Euromedix, Leuven, BelgiumResting energy expenditure will be measured using the Q-NRG, Cosmed Benelux B.V., Nieuwegein, The Netherlands. Patient satisfaction will be measured via the Diabetes Treatment Satisfaction Questionnaire (DTSQ) [28, 29]Attitudes towards using eHealth (general and specific for this diet app) to access health information, measured via the eHealth Impact Questionnaire (EHIQ) [30]Depression and anxiety via the Hospital Anxiety and Depression Scale (HADS) [31]Adherence will be measured with log-on information of the appCompliance with the diet will be measured by analysing dietary history (energy intake compared to advised energy intake in %)Attrition will be measured by the number of participants that drop-out (categorised by reason for drop-out). Practical use of the intervention diet-app, via self-developed questionnaire, focus groups, and the System Usability Scale (SUS) [32]Demographic variables, drug use, smoking and drinking habits, exercise, and medication use will be measured using a self-developed questionnaire.

### Plans to promote participant retention and complete follow-up {18b}

Patients will receive a notification in the app (intervention group) or via mail (control group) of research appointments. They will also be notified if questionnaires are not completed on time. Also, when patients are not active in the app for the first 1 to 2 weeks, the patient is contacted to see if there is an issue with the app that can be resolved. When patients do not show up for their appointments, they will be contacted by phone to find out the reason for their absence. Their appointment will be rescheduled if possible.

### Data management {19}

Data will be entered into a data management system (Castor EDC®, Amsterdam, The Netherlands) with a consecutive code number (no initials or date of birth). All original paperwork, including informed consent, will be kept in a locked room/closet at the primary study site. All data, digital and on paper, will be kept for a maximum of 15 years after the study has finished.

### Confidentiality {27}

The subject identification code list, which links the code number to the participant, will be safeguarded by the coordinating researcher in a ‘master file’. The key to the code is only accessible by the investigators. Study data can only be accessed by the investigator team, staff of the Health Care Inspection and members of the Medical Ethical Committee, as stated in the informed consent form. The handling of personal data will comply with EU General Data Protection Regulation and the Dutch Act on Implementation of the General Data Protection Regulation.

### Plans for collection, laboratory evaluation, and storage of biological specimens for genetic or molecular analysis in this trial/future use {33}

We will collect samples of fasted blood (serum and plasma) for study purposes only. The other laboratory measurements are part of routine care. These blood samples will be encoded and stored at − 80 °C until analysis. All blood samples will be kept for a maximum of 15 years after the study has finished.

### Statistical methods

#### Statistical methods for primary and secondary outcomes {20a}

All analyses will be conducted according to the intention-to-treat principle. Normality of the data and homogeneity of variances will be tested using Shapiro–Wilk test and Levene’s test. As measures of central tendency for numerical data, we will use the mean (in case of normal distribution) and median values (in case of non-normal distribution), with respectively the standard deviation and interquartile range as measures of dispersion.

The primary endpoint will be defined as the between group difference in relative weight change during 12 months. The relative weight change will be analysed with a general linear model for repeated measurements, with independent variables treatment arm, time point (T1, T2, or T3), hospital, and the interaction between treatment arm and time point. The within patient correlations will be modelled using an unstructured covariance matrix. The estimated difference between treatment arms (intervention minus control) in the relative weight change at T3 (12 months) will be calculated using the estimated marginal means. Non-inferiority will be concluded if the upper limit of the 95% confidence interval of this estimated difference remains below the stated non-inferiority margin of 3.0%. When non-inferiority has been demonstrated, the costs and effects will be expressed in the savings per percent weight reduction/patients who successfully lost weight, by means of a probabilistic model, so that the likely skewed data on costs can be considered.

For the secondary analyses of the efficacy outcomes cardiovascular risk factors (lipids), quality of life (EQ-5L), patient satisfaction (DTSQ), attrition (drop-out), and compliance (log-on information and kcal intake vs advised), we will use analysis of covariance (ANCOVA) models. The dependent variable in these models will be the outcome at T1, T2, or T3, and the independent variables will be treatment arm, the outcome at baseline (T0), and hospital. The secondary analyses are exploratory in nature as the power calculation is based on the primary outcome.

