### Trial design {8}

This study is a randomised, controlled, non-inferiority multi-centre trial with a duration of 1 year. After signing informed consent, eligible participants will be randomised 1:1 to the intervention (E-VLED) or control (VLED) group. Outcome parameters will be measured at baseline, 2 months, 4 months, and at 1 year. In Fig. 1, we show the flow chart of this study.

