### Sample size {14}

In our previous study using the same diet intervention [5], the standard deviation of the difference in weight loss at 12 months was 7.58 kg, and the baseline weight was 105 kg; thus, the standard deviation percentage weight loss was 7.2%. In the field of long-term weight loss, two weight loss percentages are considered clinically relevant, 3% and 5% [22–24]. In order to stay on the safe side, we choose the non-inferiority margin based on the lower of these two percentages, i.e. a non-inferiority margin of 3%. Results of recently published randomised controlled trials on dietary eHealth interventions [25, 26] have yielded estimates for the percentage weight loss due to these interventions. In light of these results, we assumed in the power analysis that the weight loss percentage is 2% greater in the intervention arm than in the control arm. This estimate of 2% was obtained by averaging the results of Katula et al. (− 3.4%) and Baer et al. (1.1%). Based on a one-sided alpha of 0.025, power set at 0.80, we calculated that at least 33 participants in each study group are required for the present study (calculated using R). Anticipating a drop-out of 20%, based on attrition data of the POWER study, we aim for the inclusion of 80 participants (40 participants per group).

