### Assignment of interventions: allocation

#### Sequence generation {16a}

Eligible patients who signed informed consent will be randomly assigned to either the intervention group or the control group in groups of ten patients. This means that patients who have given informed consent will be randomised only when a group of ten patients is reached, who will then all be in the same treatment group. The 8 groups of ten patients will be randomised with an allocation ratio of 1:1, using blocked randomisation with stratification by centre. The initial block size per centre is two groups (i.e. 10 patients per randomisation arm), and in two of the three centres, there will be a second block of one group. The randomisation, according to a random block design stratified to study site, is supervised by JR and is blinded for the researcher/dietician recruiting and/or performing the intervention. The randomisation is computer controlled.

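### The primary model omits baseline weight, a free covariate that would probably bring a modest gain in precision and conditional protection against chance imbalance

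*Protocol article*

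**What the plan says.** All references are to the Protocol article.

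- **Endpoint** (Statistical methods {20a}): "The primary endpoint will be defined as the between group difference in relative weight change during 12 months".
- **Primary model** (same section): "The relative weight change will be analysed with a general linear model for repeated measurements, with independent variables treatment arm, time point". The complete covariate list reads "with independent variables treatment arm, time point (T1, T2, or T3), hospital, and the interaction between treatment arm and time point", and the covariance matrix is unstructured. Baseline is not one of the modelled time points, so the covariance structure does not condition on it either.
- **Secondary models** (same section): ANCOVA, in which "the independent variables will be treatment arm, the outcome at baseline (T0), and hospital". No reason is given for treating baseline differently.
- **Availability of baseline weight** (Trial design {8}): "Outcome parameters will be measured at baseline, 2 months, 4 months, and at 1 year". The weight row of Table 1 is marked at T0.
- **Allocation** (Sequence generation {16a}): "The 8 groups of ten patients will be randomised with an allocation ratio of 1:1, using blocked randomisation with stratification by centre". Centre is the only stratification factor.
- **Variability** (Sample size {14}): "the standard deviation percentage weight loss was 7.2" percent.
- **Subgroup models** (Methods for additional analyses {20b}): the sex and ethnicity models add interaction terms to the primary model, so they take over its covariate list.

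**The concern.** Baseline weight enters the primary analysis only as the denominator of the percent change. That is not the same as adjusting for it. Unless follow-up weight is proportional to baseline weight, percent change still varies with baseline weight. That leaves removable variance in the residual. It also means that, given the imbalance that actually occurs, the estimated arm difference is shifted.

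At stake is some width of the confidence interval that is compared with the 3-point margin, and the credibility of the estimate if the arms happen to differ in starting weight. The covariate list is written out in full, so this is a choice the article fixes and not a detail left to an analysis plan.

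**Working it through.** **Inputs from the article** (Sample size {14}): SD of percent weight loss 7.2 (7.58 / 105 = 7.22%); margin 3 points; assumed true difference 2 points in favour of the intervention; one-sided alpha 0.025; power 0.80; 33 per arm.

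**Input not in the article:** the correlation r between percent change and baseline weight. Assumed |r| = 0 to 0.4.

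**Step 1: reproduce the stated sample size.** The distance from the assumed truth to the margin is 3 + 2 = 5 points.

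n per arm = 2 × (1.960 + 0.842)² × 7.2² / 5² = 2 × 7.85 × 51.84 / 25 = 32.6, rounded up to 33.

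This matches the article (a t-based calculation gives 34). The calculation uses the unadjusted SD.

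**Step 2: add baseline weight as a covariate.** The residual SD becomes 7.2 × √(1 − r²). Power at 33 per arm is Φ(5 / [SD × √(2/33)] − 1.96), and the 95% interval half-width is 1.96 × SD × √(2/33).

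| \|r\| | Residual variance | Residual SD | n per arm for 80% power | Power at 33 per arm | Half-width (points) |
|---|---|---|---|---|---|
| 0 | 100% | 7.20 | 33 | 80.5% | 3.47 |
| 0.1 | 99% | 7.16 | 33 | 80.9% | 3.46 |
| 0.2 | 96% | 7.05 | 32 | 82.1% | 3.40 |
| 0.3 | 91% | 6.87 | 30 | 84.1% | 3.31 |
| 0.4 | 84% | 6.60 | 28 | 86.8% | 3.18 |

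**Step 3: is that range of r plausible?** Let b be the slope of 12-month weight on baseline weight. Assume mean weight at 12 months is 92% of a 105 kg baseline. Near the mean, percent change then varies with baseline weight at about 100 × (b − 0.92) / 105 points per kg, which is zero only at the proportional slope b = 0.92. With an assumed baseline SD of 20 kg and b = 0.8, this is −0.114 points per kg, so r ≈ −0.114 × 20 / 7.2 = −0.32 (simulation: −0.31). At b = 0.93 the simulated r is 0.02. Over assumed baseline SDs of 15 to 25 kg and slopes of 0.8 to 1.0, with the SD of weight change held at 7.58 kg, simulated |r| ran from 0.02 to 0.38. Dividing by baseline thus removes part of the dependence, and how much remains depends on quantities the article does not report.

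**The case against.** The best defence is that baseline is already used. The secondary outcomes are modelled as raw values, so baseline has to enter as a covariate, whereas the primary outcome is a change relative to baseline. Both are conventional. The contrast also applies only to secondary outcomes with a T0 value; drop-out and app log-on data have none. This stands as a limit on the inconsistency. It does not show that percent change does the work of a covariate, because that needs proportionality.

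The size also rests on an assumed correlation, which may be close to zero. That stands too.

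Three stronger readings are tempting, and the article does not support them.

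- **Imbalance as an extra threat measured against the margin.** At 40 per arm the standard error of the difference is 7.2 × √(2/40) = 1.61 points. One standard error of baseline imbalance shifts the contrast by r × 1.61, or 0.16 to 0.64 points for r = 0.1 to 0.4. A reader might set this against the 3-point margin as a further risk. It is the same effect as the variance loss: the unadjusted contrast is unbiased over the randomisation, and chance imbalance is already part of its standard error. What adjustment adds is protection conditional on the imbalance observed.
- **Imbalance by selection.** All ten participants consent before the group's allocation is requested (Sequence generation {16a}, Concealment mechanism {16b}), and the article describes nothing that would select by weight. Whether allocations in small blocks can be predicted is a question about concealment, which a covariate would not settle.
- **A trial short of power.** The stated 33 per arm reproduces. Forty per arm less 20% leaves 32, with about 79% power on the article's own inputs. The missing covariate does not make the sample size wrong.

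Finally, each group of ten consists of patients "who will then all be in the same treatment group". A patient-level covariate does not account for the resulting within-group correlation, so this point should not borrow weight from that one.

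**Conclusion.** The point holds as a recommendation for a free improvement. The primary model omits a covariate that is collected at T0 and used in the secondary models wherever a baseline value exists, and percent change does not fully replace it. For |r| of 0 to 0.4, the loss is 0% to 16% of residual variance, equivalent to between 0 and about 6 percentage points of power at 33 per arm (86.8 − 80.5 = 6.3). At |r| = 0.3 it is 3.5 points of power, and the interval half-width falls from 3.47 to 3.31.

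The omission itself is certain, because the covariates are listed. The size is not, because r is assumed; it is probably modest, since the outcome is already scaled by baseline. The power figures also treat participants as independent, as the article's own calculation does. The planned analysis is not invalid for lack of this covariate.

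**What to change.** In Statistical methods {20a}, add baseline weight as a fixed effect in the primary repeated-measures model, preferably with its interaction with time point so that its relation to percent change may differ between visits. Estimate the 12-month arm difference at the mean baseline weight. The sex and ethnicity models in {20b} are built on the primary model and inherit the change.

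The cost is one sentence and, with three post-baseline time points, three parameters (one main effect and two interaction terms). No data are added and no participant is lost, because percent change cannot be calculated without the baseline weight. The main effect alone would already meet most of the point. The change should be written down before the outcome data are examined by arm; added later, it could look data-driven. The correlation within randomised groups of ten needs its own solution.

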**Methods:**

We will conduct a randomised, controlled trial with non-inferiority design in patients with type 2 diabetes and obesity (BMI > 30 kg/m^2^), aged 18–75 years. The control group will receive the usual care VLED intervention, while the intervention group will receive the E-VLED intervention for 1 year, where face-to-face contact will be partly replaced by an eHealth (mobile) application. The main study endpoint is the difference in weight (% change) between the control and intervention group after 1 year, plus the difference between the total costs (euro) of the treatment in the control and intervention groups. The secondary aims are to investigate the effectiveness of the E-VLED diet intervention regarding cardiovascular risk factors, quality of life, patient satisfaction, compliance, and to study whether there is a difference in effectiveness in pre-specified subgroups. General linear models for repeated measurements will be applied for the statistical analysis of the data.

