**Discussion:**

We hypothesise that the E-VLED intervention will be equally effective compared to the usual care VLED but lower in costs due to less time invested by the dietician. This will enable to help more people with type 2 diabetes and obesity to effectively lose weight and improve their health-related quality of life.

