## Objectives {7}

The primary objectives of this study are as follows:To determine if an E-VLED intervention is equally effective as the usual care VLED in reducing weight after one year in people with T2D and obesity, andTo determine if an E-VLED intervention is lower in costs than the usual care VLED.

The secondary objectives of this study are as follows:To determine the effectiveness of an E-VLED intervention regarding cardiovascular risk factors and quality of life, compared to a VLED interventionTo determine the effectiveness of an E-VLED intervention regarding patient satisfaction and attrition/compliance, compared to a VLED interventionTo determine if there is a difference in effectiveness and patient satisfaction of an E-VLED intervention between males and femalesTo determine if there is a difference in effectiveness and patient satisfaction of an E-VLED intervention between participants of different origins

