#### The intervention group

The eHealth application, which replaces part of the face-to-face contacts, will only be used by the intervention group. In-person contact will be limited to one individual intake meeting and three group meetings. The eHealth application is a mobile diet app, which was developed earlier and has already been pilot tested. In this app, the steps of the diet-intervention will be explained via text and infographics. Participants will receive recipes and tips useful for the different stages of the diet. Exercise is encouraged with personal goal setting, using the national guidelines for exercise [18], and challenges. Personal goal setting with respect to diet, exercise, weight, body composition, glucose levels, medication use, physical complaints, and quality of life will be used and monitored within the app. Moreover, participants will receive daily motivational messages to keep them on-track. To make the app more interactive, the participants can use a chat-function with the dietician, once a week for the first 10 weeks; thereafter, the dietitian will be available every other week for the chat feature in the app. The app is end-to-end encrypted, according to the national privacy guidelines.

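### Lower cost is an unconditional primary objective, but the only stated cost analysis runs only if non-inferiority is shown, and it reports a ratio rather than the euro difference

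*Protocol article*

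**What the plan says.** Objectives {7} gives two primary objectives. The second is to "determine if an E-VLED intervention is lower in costs than the usual care VLED", with no condition attached. The abstract (Methods) puts costs in the main endpoint alongside weight: "plus the difference between the total costs (euro) of the treatment in the control and intervention groups". Outcomes {12} lists the cost difference as a main study parameter made up of treatment, health-care and production-loss costs, again without condition.

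Statistical methods {20a} reads differently. It defines the primary endpoint as weight change alone, and its one sentence on costs begins: "When non-inferiority has been demonstrated, the costs and effects will be expressed in the savings per percent weight reduction/patients who successfully lost weight". It goes on to say that this is done "by means of a probabilistic model, so that the likely skewed data on costs can be considered". It does not say what happens to costs if non-inferiority is not shown.

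The article gives two values for the expected weight effect. The abstract (Discussion) states: "We hypothesise that the E-VLED intervention will be equally effective compared to the usual care VLED but lower in costs". Sample size {14} states: "we assumed in the power analysis that the weight loss percentage is 2% greater in the intervention arm than in the control arm".

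**The concern.** Two things do not fit together.

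- **The condition.** A question posed unconditionally as primary has a stated analysis that depends on the result of the other primary question. If non-inferiority is missed, the trial has no stated route to an answer on cost. That is also a case where cost information matters: a cheaper programme that may be slightly less effective is a trade-off a payer must weigh.
- **The quantity.** The objective and main parameter are a difference in euros. The analysis yields savings per percent weight reduction, or per patient who succeeds, which is a different quantity. The article does not say whether the ratio is incremental (between arms) or within arm, and the two behave very differently.

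Conditioning on non-inferiority also means that the cost-effect result is seen only when the weight estimate happens to be favourable enough.

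**Working it through.** **Inputs from the article.** SD of percentage weight change: "thus, the standard deviation percentage weight loss was 7.2" (%). Margin 3 points, one-sided alpha 0.025, power 0.80, assumed difference 2 points in favour of E-VLED, 33 evaluable per arm, 40 per arm recruited, 20% drop-out (all Sample size {14}). Decision rule: upper 95% limit of intervention minus control below 3.0 (Statistical methods {20a}). Negative differences favour E-VLED.

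**Reproducing the plan's figure.** n = 2 × 7.2² × (1.960 + 0.842)² / (3 + 2)² = 103.68 × 7.849 / 25 = 32.6, so 33 per arm, as stated.

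**How often the condition fails.** SE = 7.2 × √(2/33) = 1.77. Non-inferiority needs an estimate below 3 − 1.96 × 1.77 = −0.47. P(shown) = Φ((−0.47 − δ)/1.77), where δ is the true difference.

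| True difference δ | P(shown) | Condition fails | Mean estimate when shown |
|---|---|---|---|
| −2 (planning assumption) | Φ(0.86) = 0.805 | 19.5% | −2.61 |
| −1 | Φ(0.30) = 0.617 | 38.3% | −2.10 |
| 0 (equal effectiveness) | Φ(−0.27) = 0.395 | 60.5% | −1.73 |

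The last column is the mean of a normal distribution truncated at −0.47: δ − SE × φ(z)/Φ(z), with z = (−0.47 − δ)/SE. At δ = 0 this is −1.77 × 0.385/0.395 = −1.73.

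**Sensitivity to numbers.**
- With 32 per arm (40 less 20%), SE = 1.80 and the threshold is −0.53. Failure is about 21% at −2 and 62% at 0.
- With 40 per arm and no drop-out, SE = 1.61. Failure is 13%, 30% and 54% at −2, −1 and 0.
- Whole groups of ten are randomised (Sequence generation {16a}). The article gives no intraclass correlation. For an assumed 0.02 to 0.05 and 33 per arm, failure becomes 25–32% at −2 and 65–70% at 0.

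**The ratio's denominator, at 33 per arm.**
- *If incremental:* before any condition is applied, it is centred on zero at δ = 0. At δ = −2 it is 2/1.77 = 1.13 SE from zero, with a 13% chance of the wrong sign.
- *If within arm:* SE = 7.2/√33 = 1.25. For an assumed loss of 5–10%, it is 5/1.25 ≈ 4 to 10/1.25 ≈ 8 SE from zero, so it is stable.

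**The case against.** **The sentence may govern only the joint display.** It conditions how costs and effects are expressed together, and the cost difference is listed elsewhere as a main parameter without condition. A plain estimate of it may sit in a full protocol or SAP that is not shown. This is fair, and its absence alone would be no finding. What stands is that the article does state a cost analysis, does attach a condition to it, and announces no hierarchy in the objectives or outcomes that would explain the condition.

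**Ordered testing can be legitimate.** A formal claim of lower cost may properly wait for non-inferiority. That justifies ordering the claims; it does not justify withholding the estimate.

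**Equality is not the planning assumption.** Correct: 60% is the figure under the stated hypothesis and 20% the figure under the sample-size assumption. The article uses both values, so both belong in the range.

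Three stronger readings are tempting but not supported:

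- *A reader might infer that the denominator is near zero by design.* The sample size assumes 2 points, and the text does not say the ratio is incremental. Once the condition is met, an incremental point estimate is always below −0.47, although its interval may still include zero.
- *A reader might infer that the selection overstates cost-effectiveness.* For a fixed saving, an inflated weight difference shrinks savings per percent: dividing by 2.61 rather than 2 lowers the ratio by 1 − 2/2.61 = 23%. Any bias in euros depends on a correlation between cost and weight that the article does not give.
- *A reader might infer that E-VLED takes more dietitian time*, from chat offered "once a week for the first 10 weeks; thereafter, the dietitian will be available every other week". If it runs to week 52, that is up to 10 + 42/2 = 31 occasions. This is a ceiling on availability, not workload, and control participants also receive calls after group sessions and extra contacts for glucose regulation. Outcomes {12} does list treatment costs as a separate component.

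**Conclusion.** The point holds in this form. A primary objective stated without condition has, as its only described analysis, one that is conditional on non-inferiority and that reports something other than the euro difference. Followed as written, the rule leaves the cost question without its stated analysis in about 20% of trials at the planned 2-point advantage, 38% at 1 point and 60% at equality. These figures assume 33 evaluable per arm, SD 7.2, a normal approximation and no clustering; clustering would raise them.

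When the condition is met, the weight estimate is selected in favour of E-VLED: on average −2.6 if the truth is −2, and −1.7 if it is 0. This is a bias in the weight effect only. An incremental ratio would be poorly determined and a within-arm ratio would not; the text must say which is meant. The planned probabilistic model is justified by skewed costs, and nothing in the article suggests it deals with the condition or with an uncertain denominator.

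**What to change.** In Statistical methods {20a}:

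1. Delete the condition on non-inferiority. If a formal claim of lower cost is to follow non-inferiority in a fixed order, state that separately; the estimate is reported either way.
2. Name the between-arm difference in mean total costs (euro), with a 95% interval, as the primary cost result, in all randomised participants and whatever the weight result.
3. Use a method that allows for skewed costs and for the randomised groups of ten. With eight groups, about four per arm, a bootstrap that resamples groups is not reliable; a model with a group effect and a small-sample correction is one option.
4. Show joint cost-effect uncertainty on a cost-effectiveness plane, or as net benefit over a range of willingness to pay per percent weight loss. The article gives no basis for a single value, so a range is needed.
5. If the ratio is kept, make it secondary, say whether it is incremental or within arm, and define successful weight loss.

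The cost is a change of wording and a little more analysis. No additional participants or measurements are needed. The interval for the cost difference may be wide with so few groups, and should be reported as such.
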